#### Secondary outcome measures

The following secondary outcomes will be assessed in web-based self-administered questionnaires:

• Quality of life is assessed with the 12-item Short Form Health Survey (SF-12) [39], measured at baseline and after 3 and 12 months. The EuroQol (EQ-5D) [40] will be administered at baseline and after 3, 6 and 12 months. This questionnaire assessing the current health status consists of 5 dimensions (mobility, self-care, usual activities, pain/discomfort, and anxiety/depression), each with 3 levels.

• Treatment satisfaction is assessed with the Diabetes Treatment Satisfaction Questionnaire status and change version (DTSQs and DTSQc) [41-44]. The 8-item questionnaires, measure treatment satisfaction and how this satisfaction has changed on 7-point Likert scale. It will be used as an evaluation instrument of the intervention and will be measured at baseline, 3 and 12 months.

• Self-efficacy beliefs are assessed with the Confidence in Diabetes Self Care. This is a 21-item questionnaire, measuring the level of confidence a diabetes patient has in performing self-care activities on 5-point Likert scale [45]. It will be measured at baseline, 3, 6 and 12 months and will be used in evaluating the theoretical background.

• Illness perceptions are assessed with the brief Illness Perception Questionnaire (brief-IPQ). This is a 9-item questionnaire assessing the five core dimensions of illness representations (illness identity, timeline, personal control, treatment control, cause) according to Leventhal's theory of self-regulation [46]. It will be measured at baseline, 3, 6 and 12 months to determine changes in patients' representations regarding diabetes and its controllability and will also be used in evaluating the theoretical background.

• The patient-reported number of hypoglycaemias will be measured by means of a hypoglycaemia diary in which the patient report the severity of each event, glucose value, self-treatment and need of assistance.

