**Methods/Design:**

T2DM patients (n = 248), aged 35–75 years, with an HbA1c ≥ 7.0%, eligible for treatment with insulin and able to use the internet will be selected from general practices in two different regions in the Netherlands. Cluster randomisation will be performed at the level of general practices. Patients in the intervention group will use a self-developed internet programme to assist them in self-titrating insulin. The control group will receive usual care.

Primary outcome is the difference in change in HbA1c between intervention and control group. Secondary outcome measures are quality of life, treatment satisfaction, diabetes self-efficacy and frequency of hypoglycaemic episodes. Results will be analysed according to the intention-to-treat principle.

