### Objectives

The primary objective of the study is to determine the effect on glycaemic control (HbA1c) of a patient-centred web-based insulin-titration programme in suboptimal controlled T2DM patients starting insulin treatment.

Secondary objectives are to assess the effects of the intervention on frequency of hypoglycaemic episodes, illness perceptions, self-efficacy, treatment satisfaction, and quality of life.

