#### Intervention group

When informed consent is given, patients in the intervention group will receive individual education on diabetes in general, all aspects of insulin treatment, the use of a self-monitoring device, the importance of self-monitoring, and aspects of hypo- and hyperglycaemia. In addition, information about diabetes in general and its management is available on the trial website (provided by [38]), an online education programme developed by the University of Maastricht and the Academic Hospital Maastricht, the Netherlands). The education will be given in two sessions (with an interval of 1 or 2 weeks) by the GP or practice nurse in general practices using a standard protocol provided by the investigators. The patients will receive a manual how to use the internet programme.

The internet programme is accessible through a log-in procedure, requiring a log-in name and a password. The programme is not accessible for the control group or others without permission. In case of problems, patients can always contact their practice nurse or GP, who do have access to the online data of their patients.

Patients will start with 10 IE insulin glargine. The next day, a patient has to log-in in order to start the internet programme, that consists of an online-diary with computerized algorithms. Feedback will be given on fasting blood glucose (FBG) measurements that have to be completed in the diary. The programme will reply with an insulin dose advice when two FBG measurements (on two successive days) are inputted (+ 4 IE when FBG exceeds 10 mmol/l for 2 consecutive days; + 2 IE when FBG is between 7–10 mmol/l for 2 consecutive days; – 2 IE when FBG is between 2.5–4 mmol/l for 2 consecutive days; – 4 IE when FBG is below 2.5 mmol/l for 2 consecutive days). In case of a high or low FBG level, the programme will also respond with a feedback question, guided by the self-regulation theory. According to the patients' answer, advice will be given on the concerning item (e.g. adjustment of diet or increase of physical activity). Feedback will also be given visually in colours, tables and graphics.

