The process of using the online-diary will continue until the patient has reached a normal FBG (FBG between 4.0 and 7.0 mmol/L). At that point he/she is advised to make a 5-point day-curve. Dependent on the value of one of the measured glucose values, the internet programme will automatically respond with a feedback question or will give advice to repeat the day-curve after 2 days. When a stable insulin dose is reached (all measurements are within the range of 4.0 – 9.0 mmol/L), it is advised to measure FBG once a week. When repeated day-curves (4 day-curves in approximately one week) are not within normal range, it is advised to contact the GP or practice nurse. Protocols for how to act in different situations will be provided to the GP's. If another or additional (short-acting) insulin is started, patients will not be able to use the internet programme any longer. This is also the case if the insulin dose exceeds 80 IE. If the GP or practice nurse needs extra advice, a diabetes nurse from the Diabetes Research Center can be contacted.

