#### Control group

Patients in the control group will receive individual instructions with regard to insulin dose-adjustments from their GP or practice nurse as usual. The number or type of contacts might differ per practice. The titration scheme of insulin glargine will be determined by the GP or practice nurse. Because there is no strict regimen, this can also differ per practice. The patients are offered access to the information provided on the trial website and for completing the web-based questionnaires only. GPs or practice nurses can contact a diabetes nurse from the Diabetes Research Center concerning questions about the insulin therapy.

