### Analysis

Descriptive statistics (means ± SD or median and inter quartile range as appropriate) will be used to describe the study sample with regard to demographics and baseline (clinical) characteristics. On the basis of an intention-to-treat analysis, differences in changes between the intervention group and control group are calculated with 95% confidence intervals at 3, 6 and 12 months for both primary and secondary outcomes.

Using *t*-tests and multiple linear regression – duly adapted for the multilevel structure of the data – we will compare changes in HbA1c, number of hypoglyceamias, quality of life, treatment satisfaction, illness and insulin perceptions and confidence in diabetes self-care scores at different time intervals between the groups, with adjustment for important prognostic factors like age, diabetes duration, medication and level of education where appropriate. Separate analyses of possible effect modifiers (i.e. age, depression, previous internet use) will be performed in order to gain a better understanding as to who benefits most from the intervention.

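### Hypoglycaemia is compared as one self-reported count although only the intervention arm has a set glucose-testing schedule, so part of any difference may come from detection

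*Protocol article*

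**What the plan says.** All references are to the protocol article.

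- **Objective and outcome.** Objectives: "Secondary objectives are to assess the effects of the intervention on frequency of hypoglycaemic episodes". The abstract lists it too: "Secondary outcome measures are quality of life, treatment satisfaction, diabetes self-efficacy and frequency of hypoglycaemic episodes".
- **Measurement.** Secondary outcome measures: "The patient-reported number of hypoglycaemias will be measured by means of a hypoglycaemia diary". For each episode "the patient report the severity of each event, glucose value, self-treatment and need of assistance". The section states no glucose threshold for a countable episode. It does not say whether a low reading without symptoms is to be entered.
- **Comparison.** Analysis: "we will compare changes in HbA1c, number of hypoglyceamias, quality of life", alongside the other scales. The prognostic factors named as examples are age, diabetes duration, medication and education.
- **Intervention arm.** "Feedback will be given on fasting blood glucose (FBG) measurements that have to be completed in the diary". Each dose advice needs readings from two days in a row. Once the fasting value is normal, "At that point he/she is advised to make a 5-point day-curve". The section foresees up to four such curves in about a week, then a weekly fasting reading when the dose is stable. Low fasting values prompt a feedback question. The flowchart notes describe an alert below 2.5 mmol/l, sent to the patient and the GP. Standardised education covering self-monitoring and hypoglycaemia is described for this arm.
- **Control arm.** No measurement schedule is given. On the titration scheme the section says: "Because there is no strict regimen, this can also differ per practice". Web access is limited to information and questionnaires.

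**The concern.** A diary count reflects two things: how often hypoglycaemia occurs, and how often it is noticed and written down. An episode with clear symptoms, or one where someone else had to help, is noticed whether or not a test was due. A low value without symptoms is known only if the patient measured at that moment. The intervention sets when its patients measure and teaches them what a low value means, while the control arm is left to local practice. This difference arises after allocation, so randomisation does not balance it, and patients are not blinded.

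At stake is how a secondary outcome is read. It is the only safety measure among the listed secondary outcomes of an insulin self-titration programme, and the Discussion foresees wide use of the programme if it proves effective. More testing could make self-titration look less safe than it is. Sparse testing in the stable phase could make it look safer.

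**Working it through.** **The plan's own figure.** The plan gives no expected rate, difference or power for hypoglycaemia. Its only calculation is for HbA1c, and it reproduces:

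- 2 × (1.2 × (1.96 + 0.84) / 0.5)² ≈ 90 per group
- design effect 1 + (4 − 1) × 0.05 = 1.15
- 90 × 1.15 / 4 = 25.9, so 26 practices per group
- 2 × 26 / 0.85 = 61.2, so 62 practices
- 62 × 4 = 248 patients

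Nothing below bears on that figure.

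**Testing set by the plan (Intervention group section)**

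| Phase | Intervention arm, readings per week | Control arm |
|---|---|---|
| Titration | about 7, if fasting glucose is measured daily | not stated |
| Repeated day-curves | up to 4 × 5 = 20 | not stated |
| Stable dose | 1 | not stated |

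The set intensity in the intervention arm therefore varies up to 20-fold (20 / 1) over follow-up. No ratio to the control arm can be formed at any phase.

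**What this could do to the count.** Assume that:

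- true rates are equal in both arms;
- *f* is the share of control-arm diary episodes found only by a measurement;
- *r* is testing intensity in the intervention arm divided by that in the control arm;
- measurement-only detection rises in proportion to the number of tests.

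With control-arm recorded rate λ, the intervention arm records (1 − f)λ + f·r·λ. So

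apparent rate ratio = (1 − f) + f × r.

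| f (assumed) | r = 0.5 | r = 1 | r = 2 | r = 3 |
|---|---|---|---|---|
| 0 | 1.00 | 1.00 | 1.00 | 1.00 |
| 0.10 | 0.95 | 1.00 | 1.10 | 1.20 |
| 0.25 | 0.88 | 1.00 | 1.25 | 1.50 |
| 0.50 | 0.75 | 1.00 | 1.50 | 2.00 |

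For example, f = 0.50 and r = 2 give 0.50 + 0.50 × 2 = 1.50. Neither *f* nor *r* is in the document. The table shows only that the distortion can go either way and disappears if f = 0 or r = 1. Proportional detection is itself a simplification, because time of day matters: a fasting reading misses an afternoon low.

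**The case against.** **Control-arm testing is unknown.** A reader might infer that control patients test less, but the document does not show this. The remark about the lack of a strict regimen concerns the titration scheme, not glucose measurement. All patients must be able and willing to self-monitor. All receive glargine, which the plan describes as adjusted on fasting values, and control titration follows national GP guidance that is not shown. What stands is that no common schedule exists, not that the schedules are known to differ in one direction.

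**There are two diaries.** A reader might assume that programme readings and alerts enter the outcome count. The online glucose diary and the hypoglycaemia diary are described separately, and nothing links them. Nor does the text say that low values are singled out by colour; colours are mentioned only as a general form of feedback. The route that remains is the patient, who sees a low value or an alert and then writes it down.

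**Symptom-free episodes may not be counted.** The outcome text does not say that they are. If they never enter the diary, the effect is nil, so the point must stay conditional.

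**Event classification belongs in the analysis plan.** Largely fair. Severity and need of assistance are already collected, and a full protocol or analysis plan may classify them. But the article does state the outcome as a number and the comparison as one of that number. A later plan can split the count but cannot equalise testing afterwards.

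**It is inherent to the design.** Testing is part of the intervention, and the Discussion accepts that usual care varies. Imposing a schedule on controls would change the comparator. This is a reason to adjust the reporting rather than the conduct.

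**Conclusion.** The point holds in a conditional form. The plan compares one patient-reported count, while set testing, low-value feedback, alerts and standardised hypoglycaemia education are described for the intervention arm only. If episodes found only by measurement are entered, the total mixes risk with detection. The illustrative range of 0.75 to 2.00 rests wholly on assumed values of *f* and *r* and on proportional detection. It is not an estimate of the bias, and no direction can be claimed.

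A reader might go further and say that the count cannot show a difference in hypoglycaemia at all, or that the safety objective goes unanswered. The documents do not support that. Detection may account for part of a difference or for none of it, and the diary already holds the item needed to look at episodes that depend little on testing. The outcome is secondary. The primary HbA1c comparison and the sample size are untouched.

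**What to change.** In the outcome and analysis text:

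1. Pre-state a between-arm comparison of episodes needing assistance, beside the total count. Need of assistance is already in the diary and is the recorded item least dependent on testing.
2. Show the remaining episodes in both arms by recorded severity and glucose value. Severity should not replace need of assistance as the main split, because unblinded patients grade it themselves. A split by symptoms cannot be promised, because symptoms are not among the diary items listed.
3. Keep low-glucose episodes in the safety report. The programme itself treats values below 2.5 mmol/l as urgent, and setting them aside could hide harm.
4. State in advance that a difference confined to non-assisted episodes may reflect testing frequency.

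The cost is a few sentences and one extra tabulation of data already collected, with no change to treatment or visits. The drawback is that assisted events are likely to be few, so their comparison will have a wide interval and may be inconclusive. That is why the total stays beside it.

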#### Other data collection

• *Patient characteristics, internet use (assessed on baseline):* demographic variables (age, gender, marital status, nationality, socio-economic state); experience in use of the internet; smoking (cigarettes/day) and alcohol (glasses/day) use.

• *Medication, diabetes care use:* Total required insulin dose (every 3 months this will be self-reported in the web-based questionnaire); Time delay to reach stable insulin dose (i.e. HbA1c < 7.0%); (Oral) medication changes (data obtained from pharmacy and GP); Frequency of contacts with health care providers (every 3 months this will be self-reported in the web-based questionnaire).

• *Physical and clinical measurements (assessed on the usual diabetes check-ups in the general practices every 3 months):* Weight; Length; Blood pressure; FPG; Lipid spectrum: triglycerides, total cholesterol, and HDL- and LDL-cholesterol (assessed at baseline and after 12 months).

• *Depression (assessed on baseline, 3 and 12 months):* The Patient Health Questionnaire is used to assess the general health of the patient. This brief PHQ (PHQ-9) consists of 9 items, measured on a four-point scale, in order to assess depressive disorders during the last two weeks [47]. This will be assessed because of the possible confounding effect depression has on self-performing activities.

• *Insulin Perceptions (assessed on baseline, 6 and 12 months):* Negative perceptions in insulin naive and insulin-treated patients regarding insulin treatment and changes therein are assessed with the Insulin Initiation Perception Scale (IIPS), a short version of the Insulin Treatment Appraisal Scale (ITAS) [48].

### Sample size calculation

The sample size is calculated to detect a clinical relevant difference of 0.5% in HbA1c between groups. In the Diabetes Care System West-Friesland the standard deviation (sd) of HbA1c of the general diabetes population is 1.2% [49]. A difference (d) between the intervention and control group in changes of 0.5%, a standard deviation (sd) of 1.2%, an alpha of 0.05 (two-sided), and a power of 80%, the number of patients requested in each group is 90.

Because cluster randomisation is applied at the level of general practices, the number of patients has to be multiplied with the following formula: 1 + (k-1)ρ, in which ρ is the intercorrelation coefficient (ICC) between practices. The ICC is statistically determined to be 0.05. k is the number of patients per practice that will join the study. Based on our experience, we estimate that 4 patients per practice will make the transition to insulin treatment in one year and meet the criteria of our trial. A participation of 26 general practices is needed per group:

Furthermore, taking into account a possible dropout rate of 15%, the total number of practices needed is: 2 * 26/(1–0.15) = 62, which means that 248 patients will be required.

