### Study population

The target population consists of T2DM patients (35–75 years) from general practitioners with suboptimal controlled glucose (i.e. HbA1c ≥ 7.0%) and maximal oral hypoglycaemic agents, not using insulin. Inclusion and exclusion criteria are listed in Table 1.

**Table 1 T1:** Inclusion and exclusion criteria

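### The sample size uses a cross-sectional SD of HbA1c from a general diabetes population as the SD of change in patients starting insulin, so the 80% power is unsupported for an unadjusted change score; baseline adjustment would largely repair this

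*Protocol article*

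**What the plan says.** All references are to the protocol article.

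- *Sample size calculation*, source of the SD: in a regional diabetes care system, "the standard deviation (sd) of HbA1c of the general diabetes population is 1.2"%.
- *Sample size calculation*, use of the SD, in the next sentence: "A difference (d) between the intervention and control group in changes of 0.5%, a standard deviation (sd) of 1.2"%, with "an alpha of 0.05 (two-sided), and a power of 80"%, from which "the number of patients requested in each group is 90".
- *Sample size calculation*, clustering: "The ICC is statistically determined to be 0.05", and "we estimate that 4 patients per practice will make the transition to insulin treatment in one year". With 15% dropout this leads to 26 practices per group, 62 practices and 248 patients.
- *Primary outcome measure*: the outcome is the between-group difference in HbA1c change, with HbA1c measured at baseline, 3 and 12 months.
- *Analysis*: changes are compared by t-tests and by multiple linear regression adapted to the multilevel structure. Age, diabetes duration, medication and education are given as examples of adjustment factors. Baseline HbA1c is not named.
- *Study population*: patients with "suboptimal controlled glucose (i.e. HbA1c ≥ 7.0%) and maximal oral hypoglycaemic agents, not using insulin".

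**The concern.** Two substitutions are made without comment. First, the spread of single HbA1c values between patients stands in for the spread of changes within patients. These are different quantities, linked by the correlation between baseline and follow-up. Second, a general diabetes population stands in for insulin-naive patients selected for HbA1c at or above 7.0% on maximal oral agents, all of whom start a new treatment.

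The article gives no SD of change, no correlation and no reason why 1.2% should carry over. This SD sets the number of practices to recruit, and the calculation leaves almost no slack: 90 × 1.15 = 103.5 patients needed per group, against 26 × 4 = 104 planned. At stake is whether 80% power can be claimed for the comparison that the article says it will make.

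**Working it through.** **Inputs from the article.** Difference 0.5%; SD 1.2%; two-sided alpha 0.05; power 80%; ICC 0.05; 4 patients per practice; dropout 15%. **Assumed, because the article does not give it:** the baseline to follow-up correlation r.

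**1. Reproducing the stated figures.**

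- Per group before clustering: n = 2(1.960 + 0.842)² × 1.2² / 0.5² = 90.4 (stated: 90).
- Design effect: 1 + (4 − 1) × 0.05 = 1.15.
- Practices per group: 90 × 1.15 / 4 = 25.9, so 26.
- Total: 2 × 26 / 0.85 = 61.2, so 62 practices; 62 × 4 = 248 patients.

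The chain holds. The effective number per group after dropout and clustering is 104 / 1.15 = 90.4.

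**2. What the calculation assumes about change.** With the same SD at both times, SD of change = SD × sqrt(2(1 − r)). At SD = 1.2% this equals 1.2% only when r = 0.5.

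**3. Power over a range of r symmetric about 0.5.** Power = Φ(0.5 / (SD* × sqrt(2/90.4)) − 1.96). For the unadjusted change, SD* is the SD of change. For the baseline-adjusted comparison, SD* = 1.2 × sqrt(1 − r²). The ICC is kept at 0.05 throughout. The last column is the total that would give 80% power for the unadjusted change, with the same design effect and dropout and an even number of practices.

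| r (assumed) | SD of change | Power, unadjusted change | Residual SD, adjusted | Power, adjusted | Patients for 80%, unadjusted |
|---|---|---|---|---|---|
| 0.2 | 1.52 | 60.1% | 1.18 | 81.6% | 400 |
| 0.3 | 1.42 | 65.8% | 1.14 | 83.6% | 352 |
| 0.4 | 1.31 | 72.5% | 1.10 | 86.4% | 304 |
| 0.5 | 1.20 | 80.0% | 1.04 | 89.9% | 248 |
| 0.6 | 1.07 | 88.0% | 0.96 | 93.9% | 200 |
| 0.7 | 0.93 | 95.1% | 0.86 | 97.5% | 152 |
| 0.8 | 0.76 | 99.3% | 0.72 | 99.7% | 104 |

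Worked line, r = 0.3: SD of change = 1.2 × sqrt(1.4) = 1.42; standard error = 1.42 × sqrt(2/90.4) = 0.211; 0.5 / 0.211 − 1.96 = 0.41; Φ(0.41) = 66%.

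**4. Why adjustment removes the dependence on r = 0.5.** The factor sqrt(1 − r²) never exceeds 1, so 1.2% is the worst case for the adjusted comparison if the follow-up SD is 1.2%. The adjusted variance also never exceeds the change-score variance. With baseline SD s₀ and follow-up SD s₁, the change-score variance minus the adjusted variance is (s₀² + s₁² − 2r·s₀·s₁) − s₁²(1 − r²) = (s₀ − r·s₁)², which is never negative. This does not need equal SDs.

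**5. Sensitivity to the SD itself, since the source population differs.** Assumed SDs of 1.0% and 1.4% at both times, same effective n:

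| SD | r | Power, unadjusted | Power, adjusted |
|---|---|---|---|
| 1.0 | 0.3 | 81.1% | 94.1% |
| 1.0 | 0.5 | 92.0% | 97.3% |
| 1.0 | 0.7 | 99.1% | 99.7% |
| 1.4 | 0.3 | 52.8% | 71.1% |
| 1.4 | 0.5 | 67.1% | 79.2% |
| 1.4 | 0.7 | 87.3% | 92.0% |

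An SD of 1.4% takes adjusted power below 80% at r = 0.5 and lower. The assurance from adjustment is therefore conditional on the SD.

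**The case against.** The best defence has three parts.

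*The target is first put as a difference in HbA1c between groups, and a cross-sectional SD suits a comparison of levels.* Under randomisation, differences in levels and in changes also have the same expectation. This is fair, but their variances differ. The next sentence of the calculation, the primary outcome and the analysis are all framed in changes.

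*The regression may adjust for baseline HbA1c.* The listed factors are examples, and the full covariate set is commonly left to an analysis plan, which is not shown. This lessens the concern, because under such adjustment 1.2% is the right kind of input or a conservative one. It does not remove it: the most important covariate is not named, t-tests on changes stand beside the regression, and the power is stated for changes.

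*No shortfall is demonstrated.* This stands in full. A reader might infer that the trial is underpowered, but the article gives neither r nor an SD of change, and power for unadjusted changes is 80% or more for every r from 0.5 upwards if the SD is 1.2%. A reader might also argue that varied response to insulin must widen the SD. Nothing in the article shows this. Selection at HbA1c of 7.0% or more may narrow the baseline SD and may also lower r, and the net effect cannot be settled from the text. Nor is there an error of arithmetic.

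**Conclusion.** The point holds as a fault in one design input. A cross-sectional SD from a general diabetes population is used as the SD of change in insulin starters, with no figure or argument to connect them. The claim of 80% power for an unadjusted comparison of changes is therefore unsupported, and its error may lie in either direction: about 60% to 99% for r from 0.2 to 0.8. That range assumes an SD of 1.2% at both times, an ICC of 0.05 and the planned effective 90.4 patients per group.

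It would go too far to say that the 80% is right only by coincidence. Exactly 80% needs r = 0.5, but at least 80% holds for any larger r and, with baseline adjustment, for any r. It would also go too far to promise that 248 patients suffice under adjustment whatever the population. That holds only if the follow-up SD in the trial population is no more than about 1.2%.

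**What to change.** 1. *Analysis*: name baseline HbA1c as a covariate in the multilevel regression, and make that regression, not the t-test on changes, the primary comparison.
2. *Sample size calculation*: say that 1.2% is a cross-sectional SD from a general diabetes population. Base the power on the adjusted comparison, with residual SD 1.2 × sqrt(1 − r²), and state the condition that 1.2% is the follow-up SD in the trial population.
3. Show power for 248 patients over a range of r symmetric about 0.5, such as 0.2 to 0.8, and over a range of SD, such as 1.0% to 1.4%.
4. Do not claim 80% power for the unadjusted change score unless an SD of change in patients starting insulin is cited.

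The cost is a recalculation and a few lines of text. Baseline HbA1c is already collected, and one covariate costs a negligible loss of degrees of freedom. No more patients are needed if the condition in item 2 holds; if the follow-up SD is larger, the sensitivity table shows what power remains.
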